**Methods and analysis:**

This is an ongoing single-centre randomised placebo-controlled mechanistic study (2:1 (placebo) allocation), using a multimodal neuroimaging approach, together with psychophysiological (quantitative sensory testing), genetics and questionnaire assessments. Eighty-one subjects with chronic knee OA pain are planned to power for between-group comparisons (placebo, duloxetine responder and duloxetine non-responder). Participants have a baseline assessment and, following 6 weeks of duloxetine (30 mg for 2 weeks, then 60 mg for 4 weeks), a follow-up evaluation. Brain imaging is performed at 3T with blood-oxygen-level dependent functional MRI at rest and during pin-prick nociceptive stimulation for main outcome assessment; arterial spin labelling and structural imaging (T1-weighted) for secondary outcome assessment. Questionnaires evaluate pain, negative affect, quality of sleep and cognition.

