## Background and rationale

Osteoarthritis (OA) is a major cause of long-term disability and chronic pain in the adult population. Knee and hip OA combined ranked 11th in a recent survey of global burden of disease, and symptomatic knee OA is several folds more common than hip OA.^1^ Current treatment options consist of a combination of pharmacological and non-pharmacological alternatives.^2^ Despite these options, around 20% of patients do not get satisfactory pain relief, even after undergoing joint replacement surgery.^3^ This strongly supports the notion that chronic osteoarthritis pain has a strong central component.^4–6^

Application of advanced neuroimaging tools led to novel understanding of central mechanisms underpinning acute and chronic pain states.^7^ Functional imaging in particular lends itself to the mechanistic study of analgesic treatment.^5 8–10^ Neuroimaging may also prove useful in guiding mechanism-based personalised therapy.^10–12^

To comprehensively describe brain activation states across regions and functional properties, the concept of so-called brain ‘signatures’ has emerged that can be derived from regional and network analysis of blood-oxygen-level dependent (BOLD) functional MRI data at rest or during controlled stimulation, or from cerebral blood flow maps based on arterial spin labelling (ASL) techniques.^13 14^

Duloxetine, a serotonin and norepinephrine reuptake inhibitor, has antidepressant and anxiolytic properties and is currently also used to treat chronic pain conditions. However, the precise mechanisms by which this drug acts to relieve pain are unclear and only around 50% of patients with OA have sufficient pain relief after duloxetine intake^15^; currently there is no way to predict responders.^15 16^ In healthy participants, duloxetine was found to attenuate activity in affect processing areas (amygdala, thalamus, insula and anterior cingulate cortex) while simultaneously increasing functional coupling between the amygdala and the anterior insula during an emotional face matching task.^17^ Duloxetine in major depression augmented connectivity in the anterior default mode network,^18^ while reduced connectivity within the subgenual cingulate was predictive of clinical antidepressant response.^18^

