### Data analysis

Clinical, QST and psychometric data will be compared between groups and conditions using the latest versions of statistical and image analysis software including SPSS (version 21.0).

Brain imaging data will be analysed using the latest versions of several established toolboxes: FSL (FMRIB Software Library),^28^ PyMVPA (Multivariate Pattern Analysis),^29^ Statistical Parametric Mapping V.8 (London, UK), REST (Resting-State fMRI Data Analysis Toolkit), Brain Connectivity Toolbox and GRETNA (Graph Theoretical Network Analysis)^30–32^ and LCModel (Linear Combination Model) for MRS data.^33^ All data will undergo established quality control and standard recommended preprocessing. Preprocessing steps for functional data include motion correction, slice-timing correction using Fourier-space time-series phase-shifting, non-brain tissue removal, spatial coregistration to T1-weighted image and normalisation to the MNI anatomical standard space. Spatial smoothing will be carried out using an isotropic Gaussian kernel and a high-pass temporal filtering will be applied. Next, for task-related fMRI, statistical maps will be generated for contrasts of interest, such as to identify brain activity evoked by pinprick in each individual scan using first-level general linear model.

Z-scores will be extracted from regions of interest of pain processing nodes defined from meta-analysis,^7^ emotion regulatory, default mode and salience network including anterior cingulate cortex, anterior insula, amygdala, brain stem and thalamus for both task-related and resting functional maps. Individual functional connectivity maps will be also generated. These will be used on higher level analysis which will include, among others: (1) Paired t-test to evaluate treatment effects; (2) two-sample t-test to compare groups (responders and non-responders) at baseline; (3) correlation analysis to determine associations with psychometric and QST measurements.

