### Sample size estimation

The sample size calculation was performed according to the guidelines stated by Lenth and colleagues.^34^ Estimates of change in functional activation were deduced from a duloxetine intervention study (effect size was calculated based on p values provided for the ACC).^17^ Using the Java applets,^35^ it was estimated that a one-sample, one-tailed, t-test would have 80% power at alpha of <0.005 (to allow for 10 multiple independent tests) with approximately 19 participants per group: responders to duloxetine treatment, non-responders and placebo groups.

Based on previous experience of non-usable imaging data due to patient and/or technical factors in 10% of cases, a sample size of >22 participants per group was necessary. A further allowance for 20% dropout gives 27 participants in each group, resulting in a recruitment target of 81 participants. The study is not be powered to assess clinical efficacy.

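### The abstract claims power for between-group comparisons, but the only power calculation is for a one-sample test and gives none for the primary response-prediction comparison

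*Protocol article*

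**What the plan says.** The abstract (Methods and analysis) gives the purpose of the sample size: "Eighty-one subjects with chronic knee OA pain are planned to power for between-group comparisons (placebo, duloxetine responder and duloxetine non-responder").

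The section Sample size estimation contains the only calculation. It rests on "a one-sample, one-tailed, t-test would have 80% power at alpha of <0.005", "with approximately 19 participants per group: responders to duloxetine treatment, non-responders and placebo groups". The alpha is a Bonferroni-type level: "alpha of <0.005 (to allow for 10 multiple independent tests"). The effect is a change in activation taken from an earlier duloxetine study. Its size is not given as a number; the text says only that "effect size was calculated based on p values provided for the ACC". Allowances of 10% for unusable imaging and 20% for dropout lead to 27 per group and 81 in total.

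The primary outcomes are of two kinds. Those under Treatment mechanism are changes from the first to the second scan within responders. The one under Response prediction is a baseline difference between responders and non-responders. The Data analysis section lists a paired t-test for treatment effects and, for the second kind, a "two-sample t-test to compare groups (responders and non-responders) at baseline".

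**The concern.** A one-sample test asks whether the mean of one group differs from a fixed value. Applied to change scores it is the same as a paired t-test, so it suits the Treatment mechanism outcomes. It cannot compare two groups. At the same group size and standardised effect, a two-sample test has less power because both means are estimated.

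The abstract therefore makes a claim that the sample-size section does not back, and the gap reaches a primary outcome. Prediction of response is one of the two parts of the primary objective and the first main hypothesis. A reader who believes the trial was powered for group contrasts could take a null prediction result as evidence that no baseline marker exists, when the plan gives no basis for that reading.

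**Working it through.** **Inputs from the protocol article.** One-sample, one-tailed t-test; alpha 0.005; power 80%; about 19 per group; 10% imaging loss; 20% dropout; 27 per group (Sample size estimation). Two-sample t-test for the baseline comparison (Data analysis). The effect size is not stated.

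**Step 1. The plan's own figures.**
- Alpha: 0.05 / 10 = 0.005.
- Inflation: 19 / 0.9 = 21.1, so 22; 19 / (0.9 × 0.8) = 26.4, so 27; 3 × 27 = 81. These agree with the text.
- The 19 cannot be reproduced without an effect size, so I solved for it. One-sample power is P(T > t(0.995; n − 1)), where T is noncentral t with noncentrality d√n. With n = 19 the critical value is 2.878, and 80% power needs noncentrality 3.770, so d = 3.770 / √19 = **0.865**. Taking n as 18 or 20 gives 0.894 or 0.838.

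**Step 2. The same standardised effect in a two-sample test.** This assumes that the between-group standardised difference equals 0.865. The noncentrality is d√(n/2) on 2n − 2 degrees of freedom, at alpha 0.005.

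| Usable per group | Where it comes from | Noncentrality | Power, one-tailed | Power, two-tailed |
|---|---|---|---|---|
| 19 | after both losses | 2.67 | 49% | 39% |
| 24 | 27 × 0.9 = 24.3, imaging loss only | 3.00 | 62% | 52% |
| 27 | no losses | 3.18 | 69% | 60% |

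Under this assumption, 80% power needs 33 usable per group one-tailed or 38 two-tailed.

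**Step 3. The same raw difference instead.** The implied d is scaled by the SD of a change score, whereas a baseline comparison is scaled by the SD of a single scan. With equal variances at the two scans and correlation r between them, SD of change = SD of a single scan × √(2(1 − r)). The same raw difference then has standardised size 0.865 × √(2(1 − r)) at baseline. No value of r is given, so a range is shown for 19 per group:

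| Assumed r | Standardised difference | Power, one-tailed | Power, two-tailed |
|---|---|---|---|
| 0 | 1.22 | 85% | 78% |
| 0.3 | 1.02 | 67% | 57% |
| 0.5 | 0.865 | 49% | 39% |
| 0.7 | 0.67 | 27% | 20% |

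The figures from Step 2 are the r = 0.5 row. The same formula with 24 per group and r = 0.3 gives 80% / 72%.

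**Step 4. What the two-sample test can detect.** Solving the Step 2 power formula for d at 80% power gives d = 1.16 one-tailed or 1.25 two-tailed with 19 per group, and 1.02 or 1.10 with 24. These figures need no assumption about the true effect.

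**The case against.** The best defence is that the sample-size section does not itself overclaim. It ties "would have 80% power" to a named one-sample test, and that test is right for both Treatment mechanism outcomes. The arithmetic from 19 to 81 holds. On this view the error is one clause in the abstract. That is fair as a description of where the error sits. The clause still states what the sample size is for, and no other calculation supports it. The protocol's disclaimer about clinical efficacy does not cover imaging contrasts.

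A second objection is that 0.865 describes a drug-induced change within people, while response prediction concerns a difference between people before treatment. The document gives no effect for the latter, and Step 3 shows how far the answer moves. This stands: no single power figure can be attributed to the plan.

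A third objection is that 19 may be too few for this comparison. Baseline scans come before any dropout, the Brief Pain Inventory that defines response is completed daily, and follow-up questionnaires are collected by post from those who cannot return (Compliance). A dropout may still be classifiable. This also stands, and is why 24 and 27 are shown.

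A reader might go further and infer that the one-tailed test is an error, that the unpredictable split into responders and non-responders undermines the calculation, or that the source of the effect size is unsuitable. The document does not carry these points:
- The tail is openly declared, and the background gives a direction for activity: "In healthy participants, duloxetine was found to attenuate activity in affect processing areas", among them the anterior cingulate.
- Group sizes are described as approximate, and about half of treated patients are expected to respond. A lower response rate would be the reader's own assumption.
- The source of the effect size is disclosed and cannot be inspected here.

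**Conclusion.** The abstract and the sample-size section contradict each other. Power of 80% is shown only for a one-tailed change within one group at an implied d of about 0.86. No power is given for any between-group comparison, including the primary response-prediction outcome. This conclusion rests on the text alone.

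The size is conditional. If the between-group standardised difference equals the implied d, power stays below 80% at every group size the plan allows, from 39% (two-tailed, 19 per group) to 69% (one-tailed, all 27). If the raw difference is held equal, a low scan-to-scan correlation can bring power to 80% or above, and a high one takes it well below half. A reader might infer that the trial simply has 39% or 49% power for prediction. The document does not support that as a fact, because it states neither a between-group effect nor a correlation. Nor does it follow that the 80% is miscalculated for the within-responder outcomes, or that more participants are required.

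**What to change.** Keep 81 participants and change the text:

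1. State the effect size assumed in the calculation as a number.
2. Say that about 19 per group gives 80% power for a one-tailed within-group change of that size at alpha 0.005, and for nothing else.
3. Remove the abstract's claim of power for between-group comparisons, or replace it with a separate justification that names its assumed effect.
4. State what the responder versus non-responder comparison can detect with 80% power: d of about 1.16 one-tailed or 1.25 two-tailed with 19 usable per group, or 1.02 or 1.10 with 24. Any power figure should carry its assumption.
5. Report the between-group contrasts as estimates with confidence intervals, so that a null prediction result is not read as showing that no marker exists.

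The cost is a revision of the abstract and the sample-size section, and a less favourable statement of power. No extra participants or procedures are needed.

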### Recruitment

Identification of potential participants is done by contacting people who have taken part in previous studies within the ARUKPC. Recruitment through primary care and posters is also being used. Candidates are prescreened during phone call following expression of interest. Medical notes are verified for eligibility following oral consent. Suitable candidates are then booked in for the first visit when written informed consent is obtained from all individuals taking part in the study by one of the investigators before any interventions related to the study will take place. The procedure consists of the following: the investigator explains the details of the study and provides participant information sheet and drug information leaflet, ensuring that the participant has sufficient time to consider participating or not. The investigator then answers any questions that the participant may have concerning study participation before signing the consent form.

### Concomitant medication

Participants are instructed not to change their regular pain treatment while taking part in the study. Rescue pain medication, taken on an ‘as needed basis’, is accepted during the trial period and its use is documented in a daily pain diary.

### Compliance

Compliance is assessed in the first instance by their attendance at all scheduled research visits. Participants who choose to discontinue are asked to inform the investigators on their decision. Participants are contacted via telephone while undertaking the study medication to promote participant retention and completion of follow-up. During the second visit, participants are asked whether they took the drug according to the protocol.

Should the participant be unwilling to reschedule their appointment, data collected up until that point will be carried forward to the analysis stages and they will be withdrawn from the investigation. If a participant is unable to return for their second visit, follow-up questionnaires will be obtained by post.

### Criteria for withdrawal

Participation in this study is voluntary and participants are free to withdraw from the trial at any time, without giving any reason. However they must seek advice from the researchers before doing so as discontinuing duloxetine treatment suddenly may cause drug withdrawal effects. Involvement may be also discontinued by the investigators in case of any significant adverse effect of duloxetine/placebo treatment or when subjects require major changes to their ongoing pain management during the course of the study.

### Adverse events and data safety monitoring

All observed or reported adverse events (AEs) are recorded by the investigators. No AEs are expected in relation to the MRI scanning. Potential AEs are anticipated to be only related to drug intake. All adverse events are recorded and monitored until resolution, stabilisation or until it has been shown that the study intervention is not the cause. Any serious adverse event is recorded and reported to the research ethics committee as part of the annual reports.

### Handling and storage of data and documents

All study staff and investigators endeavour to protect the rights of the trial participants to privacy and informed consent, and will adhere to the Data Protection Act, 1998. Personal data is handled confidentially. Imaging, sample and questionnaire data are anonymised by assigning a unique participant identification code, containing the abbreviation of the study’s name followed by a sequence number. The link between study identification code and individual's personal details is kept on the consent form and MR screening form.

Computer-held data are kept securely and password protected. All data are stored on a secure dedicated server. Access to data is given to the investigators and is restricted by user identifiers and passwords. Copies of the raw imaging data are also stored on CD/DVD in a locked room in the Radiological Sciences premises as back-up data. Either double data entry or checks of 40% of data entry are to be performed to promote data quality.

Direct access is permitted when required to all source documents and other study documentation for example, signed consent forms, for the purpose of study monitoring and audit and other lawful regulatory inspection by the chief investigator, sponsor’s designee and inspection by relevant regulatory authorities.

The investigators have full access to the dataset without limiting contractual obligations.

### Monitoring trial conduct

Trial conduct is subject to systems audit of the Trial Master File for inclusion of essential documents, permissions to conduct the trial, trial delegation log, curriculum vitae of trial staff and training received, local document control procedures, consent procedures and recruitment logs, adherence to procedures defined in the protocol (eg, inclusion/exclusion criteria, correct randomisation, timeliness of visits), adverse event recording and reporting, drug accountability, pharmacy records and equipment calibration logs.

The trial coordinator or a nominated designee of the sponsor shall carry out a site systems audit according to local requirements.

10.1136/bmjopen-2016-014013.supp1Supplementary file
